10.1 Analysis Population

- Both the Intention-to-treat (ITT) and per-protocol populations will be analysed.

ITT analysis will include all participants who are randomized, regardless of protocol adherence, to ensure generalizability.

Per-protocol analysis will focus on participants who completed the study as planned, ensuring the assessment of efficacy under ideal conditions.

The trial aims to dose at least 20 participants in the psilocybin treatment arm. This number refers to participants who receive at least one 25 mg psilocybin session, not only those who are randomized.

Analyses of safety and tolerability will primarily focus on this dosed cohort.

Recruitment will continue until a minimum of 20 participants in the intervention arm have received at least one dose, unless safety or feasibility concerns require early termination.

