4.3 Primary Endpoint

- **Safety:** Incidence of adverse events (AEs) and serious adverse events (SAEs) during the trial period.

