**Clarification on Targeted Sample Size for Dosing**

The trial aims to dose at least 20 participants in the psilocybin treatment arm. This number refers to participants who receive at least one 25 mg psilocybin session, not only those who are randomized.

Analysis of safety and tolerability will primarily focus on this dosed cohort.

Recruitment will continue until a minimum of 20 participants in the intervention arm have received at least one dose, unless safety or feasibility concerns require early termination.

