**Discontinuation from the Intervention (Dosing)**

Participants may be discontinued from the intervention (i.e., psilocybin administration – first or second dose), without being excluded from the trial. Participants will be encouraged to continue with follow-up assessments unless they explicitly withdraw consent.

This approach allows for continued safety and data collection in accordance with the intention-to-treat principle.

Reasons for discontinuing intervention may include:

- Development or discovery of exclusion criteria after inclusion (e.g. new psychiatric diagnosis, pregnancy).
- Emergence of a serious adverse event (SAE) or medical condition that, in the investigator’s judgment, makes continued treatment unsafe.
- Initiation of treatment with medications prohibited according to the protocol, i.e. medications with clinically relevant 5-HT2A-receptor antagonistic properties.
- Failure to adhere to critical aspects of the study protocol (e.g. repeated missed visits, non-compliance with preparation, or safety procedures).
- Investigator decision in consultation with the medical monitor.

The reason for discontinuation is documented in the eCRF. Participants will be offered a final follow-up visit when appropriate.

- Non-compliance to fMRI will not lead to study exclusion nor discontinuation of the intervention.

7. Trial Treatments

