**All concomitant medications will be carefully documented and considered in the interpretation of clinical outcomes.**

The following psychiatric medications are prohibited in participants receiving psilocybin due to known or potential pharmacodynamic interactions and risk of attenuated psychedelic effects or adverse reactions:

•Monoamine oxidase inhibitors (MAOIs)

•Tricyclic antidepressants (TCAs)

•Benzodiazepines ≤ 2 mg lorazepam equivalents per day (must not be taken within 12 hours prior to psilocybin administration)

•Antipsychotics

•Lithium

Participants will undergo a thorough medication review during screening to identify potential pharmacological interactions. Medications with prohibited serotonergic activity require washout periods of 2–4 weeks before psilocybin dosing according to clinical practise guidelines.

- Participants who cannot safely discontinue contraindicated medications will not be included in the study.

- The washout will primarily be monitored by phone and a medical doctor within the research team appointed by the principal investigator, with in-person visits if needed. Participants who exceed the 8-week limit without dosing will be re-evaluated for eligibility by the principal investigator. The time from screening to first dosing shall not exceed 8 weeks regardless of washout status.

- Psychotherapy and other non-pharmacological treatments will be allowed throughout the study period as TAU if not deemed an exclusion criterion. Temporary daycare after discharge will be considered part of TAU rather than non-pharmacological treatment.

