10.2 Statistical Analyses

This will be an open label, two-arm, active comparator (TAU; treatment as usual), , randomized controlled, between- and within-subjects, design in up to 40 completing patients meeting DSM-5 criteria for eating disorders. The patients will be randomly allocated to the psilocybin treatment-arm. The study analyses will enable comparison of efficacy between psilocybin-treatment and treatment as usual, as well as longitudinal within-patient efficacies.

- Primary Baseline Analyses:
  The primary analyses will involve descriptive statistics for demographic and baseline characteristics, ensuring comparability across groups, and control for follow-up measurements.
- Primary Endpoints analysis
- We will analyse differences in the number of participants and severity experiencing AE/SAE between the groups standardized forms for AE/SAE capturing: Event description, Start and end dates, Severity (e.g., mild, moderate, severe), Relatedness to intervention (assessed by safety review committee), Action taken.

The primary statistical methods will be:

- Descriptive Frequencies and Percentages.
- Comparing Proportions (Most Common for "Incidence") (Chi-squared test (or Fisher's Exact Test): Fisher's exact test is preferred for small cell counts (<5).
- Risk Ratio (RR) or Odds Ratio (OR) with Confidence Intervals: Report these measures of effect size to quantify the magnitude and precision of the difference between groups. An RR > 1 would indicate a higher risk in the intervention group.
- Comparing Severity and Relatedness is assessed with Mann-Whitney U test or Student t-test to compare severity distributions between groups.
- Secondary Endpoints:
  For secondary endpoints (e.g., changes in fMRI connectivity, BDNF, rating scales), group comparisons, including t-test, ANOVA, and Repeated Measures ANOVA will be utilized. When controlling for variables such as individual differences, ANCOVA or MANCOVA will be utilized. Principal component analysis (PCA) or independent component analysis (ICA) may be applied to identify patterns in fMRI data. Task-based fMRI data will be analysed using univariate models to investigate treatment effects in syndrome-related neural circuits (Celeghin et al., 2023; Bronleigh et al., 2022). Endpoints include longitudinal between- and within-person analyses.

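### The safety analysis centres on a dosed cohort that can exist only in the psilocybin arm, while the primary endpoint is a between-arm AE/SAE comparison

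*Protocol*

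**What the plan says.** - **Primary endpoint (Section 4.3):** "Incidence of adverse events (AEs) and serious adverse events (SAEs) during the trial period".
- **Primary endpoint analysis (Section 10.2):** "We will analyse differences in the number of participants and severity experiencing AE/SAE between the groups", by chi-squared or Fisher's exact test, with an RR or OR and confidence interval.
- **Safety set (Section 10.1, and nearly word for word in Section 5.1 under the clarification on sample size for dosing):** "Analyses of safety and tolerability will primarily focus on this dosed cohort". On the target of 20: "This number refers to participants who receive at least one 25 mg psilocybin session, not only those who are randomized". Also: "Recruitment will continue until a minimum of 20 participants in the intervention arm have received at least one dose".
- **Other sets (Section 10.1):** "ITT analysis will include all participants who are randomized, regardless of protocol adherence, to ensure generalizability". A per-protocol set is planned too. Neither is linked to the safety analysis.
- **Participants whose first or second dose is withheld (Section 6.4):** they stay in the trial for follow-up. "This approach allows for continued safety and data collection in accordance with the intention-to-treat principle".
- **Delay before dosing (Section 7.3):** "Participants who exceed the 8-week limit without dosing will be re-evaluated for eligibility by the principal investigator".
- **Start of AE collection (Sections 8.2, 9.3 and 11.2):** the first dosing session.

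**The concern.** A treated-patients set in a placebo-controlled trial filters both arms by the same rule. Here it cannot. Only people randomised to psilocybin can fail to reach a dose, so the filter acts on one arm, after randomisation.

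Some of the Section 6.4 reasons for withholding a dose carry prognostic information: a new psychiatric diagnosis, a serious adverse event or medical condition, repeated missed visits. A TAU patient with the same history has no dosing step to fail and would remain in the comparison.

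If the dosed cohort supplies the psilocybin side of the Section 10.2 risk ratio, the primary contrast is no longer a comparison of randomised groups. This matters beyond the trial report. Section 5.1 says the results will guide later trials, and Sections 5.1 and 7.4 make the offer of psilocybin to controls depend on a favourable safety judgement.

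**Working it through.** **No plan figure to reproduce.** Section 10.4 sets 40 participants (20 per group) on feasibility and gives no event rate, undosed rate or power. The rates below are assumptions.

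**Step 1. How many must be randomised to dose 20.** The number is 20/(1 − d), rounded up, where d is the undosed share: 22 for 5%, 23 for 10%, 24 for 15%, 25 for 20%. At 1:1 the totals are 44, 46, 48 and 50.

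**Step 2. Shift in the RR with no true difference.** Let p be the event risk among everyone randomised, the same in both arms, and q the event risk among the undosed.

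Dosed-cohort risk = (p − d·q)/(1 − d), and RR = that risk divided by p.

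With p = 0.30 and q = 0.80:

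| d | Dosed-cohort risk | RR |
|---|---|---|
| 5% | (0.30 − 0.04)/0.95 = 0.274 | 0.91 |
| 10% | (0.30 − 0.08)/0.90 = 0.244 | 0.81 |
| 20% | (0.30 − 0.16)/0.80 = 0.175 | 0.58 |

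At d = 10% and q = 0.80, moving p from 0.20 to 0.40 moves the RR from 0.67 to 0.89. If d = 0 or q = p, the RR is 1.00. If q is below p, the RR exceeds 1.

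**Step 3. Size against sampling error.** Take 23 randomised per arm, 7 with events in each, and 3 undosed in the psilocybin arm. The 95% CI uses SE(log RR) = √(1/a − 1/n + 1/b − 1/m), for a/n versus b/m.

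- All randomised: 7/23 v 7/23, RR 1.00 (0.42 to 2.40).
- Two of the 3 undosed had events: 5/20 v 7/23, RR 0.82 (0.31 to 2.19), Fisher p = 0.74.
- All 3 had events: 4/20 v 7/23, RR 0.66 (0.22 to 1.92), Fisher p = 0.50.

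**Step 4. Whether the all-randomised denominator is enough.** AE collection starts at the first dose, a date that TAU and never-dosed participants do not have. Suppose the undosed participants' events happen before dosing and go uncollected, while all TAU events are counted. Restoring the denominator then gives 5/23 v 7/23, RR 0.71, and 4/23 v 7/23, RR 0.57. Both are further from 1.0 than the dosed-cohort values of 0.82 and 0.66. Changing the set without a common start date can therefore make matters worse.

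**Step 5. Length of the window.** Section 5.2 puts the second preparation session 7–10 days after baseline and 2–3 days before dosing, so baseline to first dose is 9–13 days (13/364 = 3.6% of 52 weeks). The time of randomisation is not stated. If it falls at screening, the window could reach 8 weeks, or 56 days.

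**The case against.** **The text can be read benignly.** The primary objective concerns the safety of psilocybin 25 mg, and describing AEs among people who took the drug is customary and proper. Section 10.1 speaks of a primary focus, not an exclusion, and also plans ITT. The sponsor may intend the dosed cohort for description and ITT for the group contrast. The assignment of sets to tables is often left to an analysis plan, which is not shown. This stands in part: the fault is not in having a dosed cohort. But Section 10.1 names it as the main safety set and Section 10.2 makes a between-group test the primary safety analysis, with nothing separating the two uses.

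**Stronger readings that the documents do not support.**
- A reader might infer that dosed patients will be set against all TAU patients. That is the natural reading, but no rule says so; the TAU safety set is undefined.
- A reader might infer that undosed people disappear. They do not: Section 6.4 keeps them in follow-up and the ITT set includes them.
- A reader might infer a large bias. With 24 randomised per arm, 6 events in each, and 4 undosed who all had events, the result is 2/20 v 6/24, RR 0.40. That is extreme for a 9–13 day window: at a constant rate, 6 events a year puts about 6 × 13/364 = 0.2 in it.
- A reader might infer that the bias always flatters psilocybin. It does so only if the undosed are at higher risk than the arm average. For acute drug effects such as anxiety, headache or nausea, the undosed are likely to be at lower risk, and the dosed-only rate is the higher one.

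**Routes to being undosed.** The 8-week limit in Section 7.3 runs from screening, so it may act before randomisation. Pregnancy and missed visits are not shown to predict AEs. Both remarks are fair, but Section 6.4 expressly covers withholding the first dose, and some of its reasons are plainly prognostic.

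**Conclusion.** The concern holds in a limited form. The protocol makes a set that exists in only one arm the primary focus of safety, and makes a between-arm comparison the primary safety analysis. Combined, these put a one-sided post-randomisation exclusion into a randomised contrast. This also sits badly with the ITT follow-up promised in Section 6.4.

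The size cannot be known from the protocol. Under the null and the stated assumptions (30% risk overall, 80% in the undosed), the RR moves to between 0.91 and 0.58 for 5% to 20% undosed. It does not move if nobody goes undosed or if being undosed is unrelated to risk. The example shifts lie well inside the confidence interval, so they would not by themselves produce a significant result. The concern bears mainly on SAEs and other less common events: if most participants have some AE, q cannot exceed p by much.

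It would also be wrong to conclude that an all-randomised analysis alone restores an RR of 1.0. With AE collection starting at the first dose, it does not.

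**What to change.** 1. In Sections 5.1 and 10.1, state that every between-arm AE/SAE test and RR or OR in Section 10.2 uses all randomised participants in their randomised arm, including those assigned to psilocybin and never dosed.
2. Keep the dosed cohort for the single-arm description of AEs after psilocybin.
3. In Sections 8.2, 9.3 and 11.2, count AEs from one common date in both arms, such as randomisation or baseline, so that TAU and never-dosed participants have a defined start and pre-dose events are captured.
4. Reconcile the safety-set wording (5.1, 10.1), the ITT follow-up statement (6.4), the AE start (8.2, 9.3, 11.2) and the primary comparison (10.2).

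The cost is wording, one more table and some extra AE recording before the first dose. Undosed participants will slightly dilute acute drug effects in the between-arm contrast, but the dosed-cohort table still shows them.

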10.2 Statistical Analyses

This will be an open label, two-arm, active comparator (TAU; treatment as usual), , randomized controlled, between- and within-subjects, design in up to 40 completing patients meeting DSM-5 criteria for eating disorders. The patients will be randomly allocated to the psilocybin treatment-arm. The study analyses will enable comparison of efficacy between psilocybin-treatment and treatment as usual, as well as longitudinal within-patient efficacies.

- Primary Baseline Analyses:
  The primary analyses will involve descriptive statistics for demographic and baseline characteristics, ensuring comparability across groups, and control for follow-up measurements.
- Primary Endpoints analysis
- We will analyse differences in the number of participants and severity experiencing AE/SAE between the groups standardized forms for AE/SAE capturing: Event description, Start and end dates, Severity (e.g., mild, moderate, severe), Relatedness to intervention (assessed by safety review committee), Action taken.

The primary statistical methods will be:

- Descriptive Frequencies and Percentages.
- Comparing Proportions (Most Common for "Incidence") (Chi-squared test (or Fisher's Exact Test): Fisher's exact test is preferred for small cell counts (<5).
- Risk Ratio (RR) or Odds Ratio (OR) with Confidence Intervals: Report these measures of effect size to quantify the magnitude and precision of the difference between groups. An RR > 1 would indicate a higher risk in the intervention group.
- Comparing Severity and Relatedness is assessed with Mann-Whitney U test or Student t-test to compare severity distributions between groups.
- Secondary Endpoints:
  For secondary endpoints (e.g., changes in fMRI connectivity, BDNF, rating scales), group comparisons, including t-test, ANOVA, and Repeated Measures ANOVA will be utilized. When controlling for variables such as individual differences, ANCOVA or MANCOVA will be utilized. Principal component analysis (PCA) or independent component analysis (ICA) may be applied to identify patterns in fMRI data. Task-based fMRI data will be analysed using univariate models to investigate treatment effects in syndrome-related neural circuits (Celeghin et al., 2023; Bronleigh et al., 2022). Endpoints include longitudinal between- and within-person analyses.
- When dichotomous (binary) outcome variables: Binary outcomes (e.g., remission, response rates) will be analyzed using logistic regression models, adjusting for baseline characteristics such as age, baseline BMI, and symptom severity. The odds ratios and 95% confidence intervals will be reported.
- When continuous (dimensional) variables (e.g., BMI, BDNF levels, cognitive flexibility) will be analyzed using linear mixed-effects models, and regression models of various types.
- Other: Exploratory Subgroup Analyses:
  Exploratory subgroup analyses will assess treatment effects across different strata (e.g., age groups, baseline severity) using interaction terms in regression models or stratified analyses to explore heterogeneity in treatment responses.
- Other: Sensitivity Analyses:
  Sensitivity analyses will address missing data using methods such as multiple imputation or maximum likelihood estimation. These methods ensure robustness of the findings by accounting for the potential impact of missing data on primary and secondary outcomes.

**Concomitant antidepressant treatment (yes/no; class; dose stability)** will be recorded and may be included as a covariate in exploratory analyses. Sensitivity analyses or subgroup analyses may be performed to explore potential moderating effects on clinical outcomes.

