4.1 Primary Objective

- To assess the safety and tolerability of psilocybin 25 mg in adolescents and young adults with anorexia nervosa.

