5.1 Overall Trial Design

- A Phase IIa, open-label, randomized controlled trial with two arms:

1. Active treatment arm; Two dosing sessions with psilocybin 25mg with psychological support alongside TAU.

2. Active comparator control arm; TAU only.

TAU includes specialized care offered in an eating disorder unit in Region Skåne, Sweden. If the active treatment arm is determined to be safe, tolerable, and preliminarily effective during the follow-up assessment, participants in the control group will have the option to switch to the active treatment while maintaining their usual specialized care.

This design minimizes ethical concerns regarding withholding a potentially effective treatment.

Participants will be randomly assigned (1:1) to either the intervention or control group.

Block randomization stratified by age group (16–17 and 18–35 years) will ensure balanced representation.

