**Statistical Consideration**

With only 40 participants, statistical power to detect between-group differences is limited regardless of blinding. Thus, the trial is appropriately focused on safety, feasibility, and tolerability. Qualitative and neurobiological measures are included to support interpretation.

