10.3 Adjustment of Significance and Confidence Interval

A Bonferroni correction or false discovery rate (FDR) adjustment will be applied for multiple comparisons to control Type I error.

Results will be presented with 95% confidence intervals, and significance will be set at a two-tailed p-value of <0.05 after adjustments.

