10.4 Sample Size Calculations

No formal power calculation has been conducted due to the pilot nature of the study. However, 40 participants (20 per group) were chosen based on feasibility and alignment with recommendations for exploratory trials in emerging therapies​.

Post-hoc power analysis will assess the adequacy of the sample size in detecting clinically meaningful changes in primary outcomes.

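### The primary safety analysis includes a between-arm test and RR/OR that are weak for uncommon SAEs at 20 per arm, and plans no interval specific to the event rate in the dosed cohort

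*Protocol*

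**What the plan says.** The primary objective (Protocol 4.1) is "To assess the safety and tolerability of psilocybin 25 mg in adolescents and young adults with anorexia nervosa". It names no comparison with TAU and no margin. The primary endpoint (4.3) is "Incidence of adverse events (AEs) and serious adverse events (SAEs) during the trial period".

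Section 10.2 turns this into a comparison: "We will analyse differences in the number of participants and severity experiencing AE/SAE between the groups". Its primary methods are:
- descriptive frequencies and percentages;
- a chi-squared test, or Fisher's exact test when cells are small;
- a risk ratio or odds ratio with confidence intervals;
- a Mann-Whitney or t-test for severity.

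Section 10.3 adds a multiplicity correction, 95% confidence intervals for results in general, and the rule that "significance will be set at a two-tailed p-value of <0.05 after adjustments".

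Section 10.1 says that safety analyses focus mainly on participants who received at least one dose, with a target of at least 20. Section 10.4 reports no power calculation: "40 participants (20 per group) were chosen based on feasibility and alignment with recommendations for exploratory trials in emerging therapies". Under Statistical Consideration in section 5.1 the protocol says "With only 40 participants, statistical power to detect between-group differences is limited regardless of blinding", and continues "Thus, the trial is appropriately focused on safety, feasibility, and tolerability".

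**The concern.** The protocol uses weak between-group power as its reason to concentrate on safety, then includes a between-group test among the primary safety methods. The power problem is just as real there, and for uncommon serious events it is severe. The quantity that the objective calls for, the event rate in people given psilocybin, is planned as a percentage, but the only intervals named in 10.2 belong to the between-arm ratios.

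The stakes are concrete. Control participants may be offered psilocybin "If the active treatment arm is determined to be safe, tolerable, and preliminarily effective during the follow-up assessment" (5.1, with 7.4), and the results are meant to guide later trials. Apart from the significance threshold, no number tells a reader what safety result would be reassuring: there is no acceptable rate, no margin and no upper bound.

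**Working it through.** **Inputs from the protocol.** 20 per group with 1:1 allocation (10.4, 5.1); two-sided 0.05 before adjustment (10.3); Fisher for small cells (10.2). The protocol states no power, event rate or effect size, so there is no figure of its own to reproduce beyond 20 + 20 = 40.

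**Assumption.** The SAE risk under TAU is not in the document. It is varied from 5% to 15%, with the psilocybin risk four times as high.

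**1. Miss rate of the test.** For each of the 21 × 21 possible outcomes (a events under TAU, b under psilocybin), take the two-sided Fisher p-value. Power is the sum of Bin(a; 20, p) × Bin(b; 20, 4p) over outcomes with p-value < 0.05. The miss rate is 1 − power.

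| TAU vs psilocybin SAE risk | Missed at 0.05 | Missed at 0.025 (illustrative: Bonferroni, two comparisons) |
|---|---|---|
| 5% vs 20% | 83% | 92% |
| 7% vs 28% | 70% | 81% |
| 10% vs 40% | 51% | 64% |
| 15% vs 60% | 20% | 28% |

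Using Fisher whenever a cell is below 5, and otherwise an uncorrected chi-squared test, gives almost the same results up to a TAU risk of 12.5%. Uncorrected chi-squared throughout would miss 71% at 5% vs 20% and 38% at 10% vs 40%.

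In observed counts, significance needs at least 5/20 against 0/20 (p = 0.047) or 7/20 against 1/20 (p = 0.044). A result of 4/20 against 0/20 gives p = 0.106. A result of 4/20 against 1/20 gives p = 0.34, with a risk ratio of 4.0 and a 95% CI of about 0.49 to 32.7.

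**2. Behaviour of RR and OR with empty cells.** With no TAU events and at least one psilocybin event, neither ratio has a finite estimate. With no events in either arm, both are undefined. The probability of no TAU events in 20 is (1 − p)^20:
- 0.95^20 = 0.36 at an assumed 5% risk;
- 0.90^20 = 0.12 at 10%;
- 0.85^20 = 0.04 at 15%.

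**3. What 20 dosed participants can exclude.** The exact (Clopper-Pearson) two-sided 95% upper limit for 0/20 is 1 − 0.025^(1/20) = 16.8%. For 1/20 the interval is 0.1% to 24.9%, and for 4/20 it is 5.7% to 43.7%.

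**4. A risk difference stays defined.** Newcombe's interval combines Wilson limits.
- The Wilson upper limit for 0/20 is z²/(20 + z²) = 3.84/23.84 = 16.1%, so 0/20 against 0/20 gives −16.1 to +16.1 percentage points.
- For 4/20 the Wilson limits are 8.1% and 41.6%. For 4/20 against 0/20 the lower limit is 0.200 − √(0.119² + 0.161²) ≈ −0.001 and the upper limit is 0.416, so about −0.1 to +41.6 points.

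The last interval shows how much harm remains compatible with a p-value of 0.106.

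**The case against.** The strongest reply is that the protocol does not lean on the test alone. Frequencies come first in the 10.2 list, ratios with intervals are included to convey precision, 10.3 promises 95% intervals generally, and 10.1 already puts the dosed cohort first. Low power and the absence of a power calculation are openly disclosed. All of this stands. It rules out saying that the primary safety result rests on the significance test.

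A reader might also infer that a non-significant result will be declared safe, or that it triggers the switch of control participants. The document does not say so. Section 7.4 leaves the switch to the safety committee's judgement, and 9.5 has that committee review safety data quarterly and after every 10 dosing sessions. Neither refers to a p-value. What remains is that nothing in the protocol guards against that reading.

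A third tempting reading is that the test misses a fourfold SAE increase at least 70% of the time without qualification. That needs a TAU SAE risk of about 7% or less. Section 9.1 counts any inpatient hospitalisation as an SAE, follow-up runs to 12 months, and the background cites relapse above 50% among those who recover. That last figure is not an SAE rate, but a TAU risk of 10% or more is plausible. For the same reason, empty TAU cells are possible but cannot be called likely. The endpoint also covers AEs, which may be far more frequent, and the miss rates above do not apply to them.

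Finally, interval methods are often left to a SAP. Here, though, the protocol itself names the primary methods and the threshold, and that choice is what fits the objective poorly.

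**Conclusion.** The point holds in a limited form. The listed primary methods give a formal role to a between-arm test and to ratio measures that suit neither the objective nor 20 per arm when the events are uncommon SAEs. They attach no specific interval to the dosed-cohort proportion, which is what the objective and 10.1 put first.

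The size depends on an assumed TAU SAE risk: a fourfold increase is missed about 83% of the time at 5%, 70% at 7%, 51% at 10% and 20% at 15%, and more often after multiplicity adjustment. These figures assume exactly 20 per arm and independent participants.

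It is a should-fix matter. The plan already includes percentages and intervals and admits its low power, so what is needed is a change of emphasis and more suitable estimators.

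**What to change.** In section 10.2:
- Make the primary safety result the proportion of dosed participants with an SAE, and with each AE class, each with an exact (Clopper-Pearson) 95% CI.
- Give the between-arm contrast as a risk difference with a score-type 95% CI (Newcombe or Miettinen-Nurminen). Keep the RR or OR and the p-values as supportive only.
- State that p>0.05 is not evidence of safety.
- State the achievable precision: 0/20 excludes only rates above about 17%, and 1/20 only rates above about 25%.

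In section 10.3, say that the adjusted significance threshold is not the criterion for the primary safety result.

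The cost is wording only, with the same participants and data. The downside is that the precision, once written out, looks less favourable than a bare statement of no significant difference.
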